## L. Definition of the Study population

For all objectives two datasets of UK primary care data will be combined: CPRD Gold and CPRD Aurum. Patients with a prescription for an oral anticoagulant in the time period 01 January 2013 to 31 January 2019 (exact cut-off date dependent on date of final data extracts) and a prior diagnosis of atrial fibrillation will be selected as the EHR cohort. Apixaban gained UK marketing authorisation in January 2013 for the indication of prevention of stroke and systemic embolism in AF patients; the minimum date is set to capture all patients prescribed apixaban for this indication in the UK. A previous study validated the use of diagnostic read codes for identifying patients with AF in CPRD by sending surveys to GPs and found a confirmation rate of 98% among patients originally identified with AF codes.

### Objective 1

**Step 1:** We will select all (HES and ONS linked) patients in the EHR cohort who would have met the following eligibility criteria for inclusion in the ARISTOTLE study, at least 6 months after patient registration in an up to standard practice: or 6 months post-UTS date, whichever is later:

- a diagnosis of AF,
- age over 18 years,
- at least one of the following risk factors for stroke: diagnosis of congestive heart failure, hypertension requiring pharmacological treatment, age greater than 75, diabetes mellitus, and prior stroke or systemic embolism,
- no AF due to reversible causes (e.g. thyrotoxicosis, pericarditis),
- no clinically significant (moderate or severe) mitral stenosis, in EHRs clinical significance and severity are not consistently recorded therefore a diagnosis of mitral stenosis will be sufficient to exclude a patient,
- no increased bleeding risk that is believed to be a contraindication to oral anticoagulation (e.g. previous intracranial haemorrhage),
- no conditions other than AF that require chronic anticoagulation (e.g. prosthetic mechanical heart valve),
- no persistent, uncontrolled hypertension (systolic BP > 180 mm Hg, or diastolic BP > 100 mm Hg), in EHRs this will be implemented by excluding patients whose latest blood pressure reading in the 6 months prior to the index date is over the systolic or diastolic blood pressure limit
- no active infective endocarditis,
- no concomitant treatment with aspirin > 165 mg/day,
- no simultaneous treatment with both aspirin and a thienopyridine (e.g., clopidogrel, ticlopidine),
- no severe comorbid condition with life expectancy of  $\leq 1$  year,
- no active alcohol or drug abuse, or significant psychosocial difficulties (e.g., psychosis, dementia),
- no recent ischemic stroke (within 7 days),
- no severe renal insufficiency (serum creatinine > 2.5 mg/dL or a calculated creatinine clearance < 25 mL/min),
- no ALT or AST > 2X ULN or a Total Bilirubin  $\geq 1.5$ X ULN (unless an alternative causative factor such as Gilbert's syndrome is identified),
- no platelet count  $\leq 100,000/\text{mm}^3$ ,
- no haemoglobin < 9 g/dL,
- no prior exposure to apixaban,
- no women who are pregnant or breastfeeding

For the 3 criteria involving patient laboratory results (renal insufficiency, low platelet count, and low haemoglobin) a patient will be excluded if their last test result in the 90 days prior to the index date meets the exclusion criteria.

**Step 2:** Next we will determine if/when these patients received apixaban or warfarin. Individuals in EHR who have more than one warfarin eligibility period within their record will be able to contribute more than once to the pool of warfarin subjects (with the covariates and person-time contributed unique to the specific eligibility period) as long as they have no past apixaban exposure.

**Step 3:** Having obtained individual level patient data for ARISTOTLE participants from Bristol Myers-Squibb we will then match each ARISTOTLE apixaban participant 1:1 with the closest available apixaban patient record in our EHR pool. We will consider matching on a selection of the following ARISTOTLE baseline characteristics:

- age
- sex
- body mass index
- systolic blood pressure (mmHg)
- history of congestive heart failure or left ventricular systolic dysfunction

[figure not shown]

- hypertension requiring pharmacological treatment
- diabetes mellitus
- prior stroke or TIA or thromboembolism
- smoking status [current smoker, former smoker, or never smoked]
- alcohol consumption [none, low, moderate, heavy]
- renal impairment [severe, moderate, mild, normal based on the CrCL value]
- prior VKA/warfarin use
- concomitant treatment with:
  - anticoagulant/VKA use other than warfarin or apixaban
  - aspirin
  - antiplatelets
  - NSAIDs
  - lipid lowering drug therapy
  - CYP3A4 inhibitors

We anticipate matching all or the majority of ARISTOTLE apixaban subjects with an EHR patient, giving us a pool of ARISTOTLE-analogous apixaban patients, with similar baseline characteristics as ARISTOTLE subjects at the point of randomisation (n~9,000).

The variables selected as potential matching variables are those known or suspected to influence the likelihood of the outcomes of interest. The exact selection of matching variables will depend on the quality and completeness of the data available and a balance will be struck between the matched sample size and sample balance. Variables may be grouped together to increase the sample size, for example by grouping concomitant medications that increase bleeding risk. Continuous variables may be coarsened by splitting into appropriate categories. A procedure will be employed to facilitate selection of a matched cohort, for example via coarsened exact matching for example by use of the %CEM SAS macro. Coarsened Exact Matching is a nonparametric matching method that has been found to give estimates of casual effects with lower variance and bias for a given sample size compared with other commonly used methods of matching.

Figure 1: Assembly of Matched Trial-analogous Cohort of EHR Patients

[figure not shown]

Step 4: The resulting trial matched sample of EHR apixaban exposed subjects will be matched to the warfarin ARISTOTLE-eligible EHR subjects (Figure 1) using a matching method such as propensity score matching (PSM), or CEM (with the final method selected based upon method giving the optimal sample size versus balance). Where an individual from EHR has multiple warfarin “eligibility periods” that can be matched to an apixaban trial matched subject, the EHR characteristics that will be matched on will be those from the beginning of the specific eligibility period. The covariates for consideration in the matching between EHR treatment arms or construction of a PS model will include the variables listed above used in in step 3 along with additional EHR variables such as data source (CPRD Gold or Aurum), socioeconomic status, and comorbidities. The hazard ratio for the outcomes of interest (listed in section N) will then be calculated. Each apixaban patient from the ARISTOTLE-eligible EHR

[figure not shown]

patients will be matched 1:1 with the warfarin EHR patient with the closest match giving a trial-analogous analysis cohort of ~18,000.

A patient may be exposed to warfarin followed by apixaban in the time period of interest and the patient be trial eligible in both treatment periods; in such a situation both patient treatment periods may be included in the EHR treatment groups with the restriction that a patient must not be matched to themselves. Given the trial exclusion criteria that a patient may not have been previously exposed to apixaban, any warfarin treatment periods after apixaban exposure would not be eligible for inclusion in the warfarin EHR cohort.

**Objective 2:** we will select patients who would not have been included in the ARISTOTLE trial (and therefore would not have been included in the Objective 1 cohort) based on their age, stroke risk factors, or presence of substantial comorbidity. Specifically, this will be patients with an AF diagnosis in the EHR cohort meeting these additional criteria:

- age >77 years (although elderly patients were not excluded the maximum age at first dose in ARISTOTLE was 76),

OR

- no evidence of at least one additional risk factor for stroke

OR

- AF due to reversible causes

OR

- evidence of drug/alcohol abuse

OR

- severe comorbid condition: ARISTOTLE required patients to be excluded from the trial if they had serious disease with a likelihood of causing death within 1 year or reasons making participation unpractical (such as dementia).

In these special patient populations the same outcomes as objective 1 will be assessed as described in section N.

**Objective 3:** we will select all patients with AF with a prescription for any anticoagulant in the treatment period from the set of treatments: apixaban, warfarin, rivaroxaban, dabigatran. For this objective all outcomes listed in section N will be assessed. Patients will be stratified on whether they would have met the ARISTOTLE trial criteria.

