| C. Technical Summary (Max. 300 words)                                                   | 
Patients with atrial fibrillation (AF) are at a greatly increased risk of stroke; prophylactic treatment with anticoagulation medication reduces this risk. In the last decade several direct oral anticoagulants (DOACs) have been approved providing an alternative to the standard treatment warfarin which has many drug and dietary interactions and requires onerous monitoring. Treatment guidelines for AF patients are based on the results from randomised controlled trials (RCT).
 
There is increasing interest in the effectiveness of medications in routine clinical practice to confirm trial results and estimate drug effectiveness in patient groups excluded from or underrepresented in clinical trials. There is however some uncertainty about the suitability of using non-interventional data to address questions about drug effectiveness and on the most suitable methods to be used. The aims of this study are to attempt to measure the association between anticoagulation treatments for stroke prevention in AF using electronic health records (EHRs) and to develop a methodological framework for using observational EHRs to answer questions about DOACs among patients excluded from or underrepresented in the RCTs.
 
This study will use individual patient data from ARISTOTLE, a pivotal trial conducted 2006-2011 in 18,201 patients that demonstrated superiority of the DOAC apixaban compared with warfarin in prevention of stroke. The individual patient data will be used to match to UK NHS patients with anonymised routinely-collected EHRs from CPRD. Analysis of drug effectiveness in this cohort will help determine whether EHR data are suitable for this kind of research question. Selecting EHR patients similar to trial patients will remove much of the variability in baseline risk of the study outcomes between trial participants and EHR patients. If we can demonstrate replication of trial results in our ARISTOTLE-analogous cohort, the same methodology will be used to determine drug effectiveness in patient groups underrepresented in the trial.
 |

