### **Rationale**

AF treatment guidelines are largely informed by randomised controlled trial (RCT) results, but we do not know if these findings apply to large patient populations not studied in trials. Apixaban is one of the most widely used anticoagulants used in stroke prevention in AF. It was studied in a large randomised trial (ARISTOTLE), but we don't know the effects of treatment in important patient groups who were not studied. Some were excluded from AF stroke prevention trials in general (e.g. those with mechanical heart valves and those with substantial comorbidity) and some are under-represented (e.g. elderly patients), meaning conclusions about these groups are difficult to make. The results we generate will firstly tell us if EHR data are suitable for this purpose. If so, our findings will aid patients, prescribers and policy makers in better understanding the benefits and risks of different anticoagulants for stroke prophylaxis in AF rather than assuming that the trial estimates are applicable to all patients.

[figure not shown]

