## F. Study Background

Atrial fibrillation (AF) is a heart condition in which the patient experiences a rapid and irregular heartbeat caused by electrical signals firing from multiple locations in the atria. Although patients may be asymptomatic, symptoms such as heart palpitations, fainting, light-headedness, and shortness of breath are reported. The prevalence of AF is estimated to be around 3% and increases with age from 0.2% in people aged 45-54 years to 8.0% in those 75 and older. The lack of organised atrial contraction in AF can lead to blood stagnating in the left atrium or left atrial appendage and the formation of thrombi. Should a thrombus move from the heart through the body this can cause systemic embolism or stroke; consequently patients with AF have a five fold higher risk of stroke. It is recommended that AF patients receive prophylactic treatment with anticoagulation medication to reduce the risk of stroke. The previous standard anticoagulation treatment for this indication, warfarin, has many treatment interactions and requires frequent monitoring and dose adjustments to stay within the therapeutic range of anticoagulant action as summarised by Hirsh et al: Warfarin has interactions with a wide range of drugs such as metronidazole which inhibits warfarin clearance, barbiturates and carbamazepine which increase hepatic warfarin, and aspirin which increases the risk of bleeding. Diet also interacts with response to warfarin with increased intake of vitamin K (present in green vegetables) leading to a reduction in the anticoagulant response to warfarin. Genetics influences the warfarin dose-response relationship most notably in common mutations in coding for cytochrome P450 (the family of enzymes responsible for warfarin metabolism). Warfarin therapy is monitored by calculating a patient's International Normalised Ratio (INR), a standardised measurement of the time taken for blood to clot. Typically for AF the patient must maintain INR at a therapeutic range between 2.0 and 3.0 with INR values below 2 putting a patient at higher risk of stroke and levels above 3 resulting in a higher risk of bleeding. On initiation of therapy INR is checked daily until in therapeutic range, then 3 times weekly for 2 weeks, then less often, according to the stability of the results. Given the challenge in maintaining INR in therapeutic range and the complex safety profile of warfarin it was hoped that the introduction of the direct acting oral anticoagulants (DOACs) would provide a safer and easier to manage long term anticoagulation therapy for AF patients. The pivotal trial of the DOAC apixaban for this indication, ARISTOTLE, demonstrated superiority over warfarin for both the primary efficacy (prevention of stroke) and safety (major bleeding) outcomes.

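### Objective 2 treats patients over 77 as outside the trial because of an unverified maximum age of 76, while Objective 1 admits the same patients as trial-eligible

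*Protocol*

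**What the plan says.** Section L defines Objective 2 as patients the trial would not have included, "and therefore would not have been included in the Objective 1 cohort". A patient enters by meeting any one of five criteria. The first is age above 77, supported by the remark that "although elderly patients were not excluded the maximum age at first dose in ARISTOTLE was 76".

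Earlier in Section L, Objective 1 Step 1 lists who counts as trial-eligible. The only age limit for entry is a lower one, "age over 18 years". At least one stroke risk factor is also needed, and the list of those includes "hypertension requiring pharmacological treatment, age greater than 75, diabetes mellitus, and prior stroke or systemic embolism". No upper limit is given.

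The Rationale says of AF stroke prevention trials that "some are under-represented (e.g. elderly patients), meaning conclusions about these groups are difficult to make". Under Objective 3, Section L stratifies patients by whether they would have met the trial criteria. The Technical Summary describes the trial as "a pivotal trial conducted 2006-2011 in 18,201 patients". The Objectives and Section L say that its individual patient data are being obtained for matching.

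**The concern.** Four of the five Objective 2 criteria correspond to a reason for which the trial's entry rules would have turned a patient away. The age criterion does not, because the protocol says in the same line that older patients were not excluded. It rests wholly on an asserted fact about who happened to enrol. Two problems follow.

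First, the age criterion conflicts with the Objective 1 list. Patients over 77 can satisfy that list, yet Objective 2 says they would not be in the Objective 1 cohort.

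Second, the asserted maximum is hard to reconcile with a large trial that had no age cap and accepted age above 75 as a qualifying risk factor.

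What is at stake is what the Objective 2 hazard ratio for this group can be said to show. Objective 2 is presented as an extension of the trial findings. If the trial enrolled people over 77, an estimate for that age group is partly replication. It would be reported as evidence for unstudied patients, and the chance to check it against the trial's own data at the same ages would be missed.

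**Working it through.** **Inputs from the protocol.** Stated maximum age at first dose, 76 (Section L, Objective 2). Objective 2 age criterion, above 77 (same place). Objective 1 age limits, over 18 with no maximum; age above 75 qualifies as a risk factor (Section L, Objective 1 Step 1). Trial size, 18,201 (Technical Summary). The protocol gives no age distribution for the trial, so the maximum of 76 cannot be reproduced.

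**Step 1: set the age rules side by side, with age in whole years.**

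| Age | Qualifies on age above 75 | Above stated maximum of 76 | Meets Objective 2 age criterion | Barred by age in Objective 1 |
|---|---|---|---|---|
| 75 | no | no | no | no |
| 76 | yes | no | no | no |
| 77 | yes | yes | no | no |
| 78 and over | yes | yes | yes | no |

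The last row is the contradiction. A patient of 78 who meets the other criteria passes Step 1, counts as trial-eligible in Objective 3, and is also assigned to Objective 2 as not included.

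**Step 2: ask whether matching removes the overlap.** If the maximum were 76 and age were matched tightly, patients over 77 would find no trial partner in Step 3. But Section L lists age only as one of the characteristics to be considered for matching, and allows continuous variables to be split into categories. With an open top band (for example, 75 and over), a patient of 80 could be matched to a participant of 76. Separation is possible but not assured.

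**Step 3: ask how demanding a maximum of 76 is.** Let p be the underlying share aged 77 or older, treating participants as independent draws. Then P(none among N) = (1 − p)^N, with N = 18,201.

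| Assumed p | Expected number aged 77 or older (N × p) | P(none) |
|---|---|---|
| 0.01% | 1.8 | 0.16 |
| 0.05% | 9.1 | 0.00011 |
| 0.1% | 18.2 | 1.2 × 10⁻⁸ |
| 1% | 182 | effectively zero |

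Setting (1 − p)^N = 0.05 gives p = 1 − 0.05^(1/18,201) = 0.000165, or about 0.016%. A maximum of 76 therefore requires an almost complete absence of people aged 77 or older from the population that enrolled. It would also mean that, in whole years, age alone could have qualified only 76-year-olds.

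As an illustration only, suppose trial ages were roughly normal. With mean 66 and SD 8, the share at 77 or older is 1 − Φ(11/8) = 8.5%. With mean 72 and SD 10, it is 1 − Φ(5/10) = 30.9%. Of the 9,120 on apixaban that is about 770 to 2,800. The means and SDs are assumptions, and the normal shape builds in an upper tail, so this shows what could be at stake and does not test the figure of 76.

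**Step 4: derive the cut-off from the stated maximum.** In whole years, a maximum of 76 puts everyone aged 77 or older outside the trial's range. The criterion that follows is age ≥ 77; the plan says above 77. Patients aged exactly 77 then enter Objective 2 only by another criterion. For scale, Section J's apixaban pool is 8,407 + 14,115 = 22,522. If 3–5% were aged 77 (an assumption), that is 676 to 1,126 patients.

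**The case against.** The best defence is that eligibility rules show who could enter and not who did. The protocol openly says older patients were not excluded and then reports what happened. Without an age distribution, nothing in the document disproves 76. This stands, and it is why the figure can only be called doubtful.

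The supporting passages are also weaker than they first look. The Rationale's remark on the elderly concerns AF stroke prevention trials in general. The Background's statement that AF prevalence "increases with age from 0.2% in people aged 45-54 years to 8.0% in those 75 and older" describes the general population and not enrolment. Neither shows that this trial enrolled anyone over 76.

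The cut-off mismatch depends on how age is measured. If the maximum is in completed years and the criterion is applied to exact age, above 77 takes in essentially everyone past the 77th birthday and does follow from 76. The protocol does not say which is used. Even in whole years, 77-year-olds are not lost to the study: they can enter the Objective 1 pool, and Objective 3 takes them regardless.

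Finally, Aim 2 covers under-represented as well as excluded patients, so an older group would still serve the study's purpose and its hazard ratio would be calculated the same way. That is fair, but it does not rescue the label. Excluded and under-represented groups support different claims, and only for the second could the trial's own data serve as a check.

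**Conclusion.** The point holds as an inconsistency in how the Objective 2 population is defined, together with an unverified figure on which that definition rests. The overlap between the trial-eligible pool and the not-included group follows from the text alone and needs no assumption about the true maximum age. The doubt about 76 rests on the trial's size, the absence of an age cap and the independence assumption. It amounts to needing an underlying share of 77-and-overs below about 0.016%.

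A reader might infer three stronger things that the document does not support:

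- **That 76 is wrong, perhaps some other summary statistic mistaken for a maximum.** No age distribution is given, and nothing points to the source of the figure.
- **That the gap between 76 and the cut-off causes studied patients to be mislabelled.** If 76 is right, a cut-off above 77 labels no studied patient as not included; it only leaves 77-year-olds unassigned, and only in whole years. Mislabelling would come from 76 being wrong.
- **That a known number of patients is affected.** The 8.5–30.9% and 3–5% shares are illustrations and not estimates.

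This should be corrected in the protocol, because the protocol itself states the figure and fixes the cut-off.

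**What to change.** Tabulate age at first dose in the individual trial data before Objective 2 is fixed, and correct the sentence if 76 is wrong. State that age is taken in completed years.

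- **If the maximum is 76:** write the criterion as age ≥ 77 in completed years and apply the same limit to the Objective 1 pool, so the two groups cannot overlap.
- **If older participants were enrolled:** keep the not-included label for ages above the observed maximum. Analyse the older ages that were represented as an under-represented, trial-eligible subgroup, and compare its estimate with the trial's for the same ages where the individual data allow.

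In either case, make the Objective 3 stratification use the same definition. The cost is one table from data the study expects to hold and a change of wording. The downside is that the not-included elderly group may become smaller.

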### **Objectives**

**Objective 1.** Check comparability of EHR data and robustness of methods for measuring AF stroke prevention medication effectiveness in EHR data by comparing with ARISTOTLE results.

We will obtain fully anonymised individual patient data from the pivotal ARISTOTLE trial. A group of individuals with similar characteristics will be selected from EHR data based on medical history, prescription data, and baseline characteristics. The ARISTOTLE trial measured the efficacy of apixaban vs warfarin for the prevention of stroke, systemic embolism, myocardial infarction, and mortality and safety (major bleeding) amongst people with AF and at least one risk factor for stroke. Individual trial participants will be matched with similar people in the anonymised EHR databases the Clinical Practice Research Datalink (CPRD) Gold and CPRD Aurum in order to create an ARISTOTLE-analogous cohort within EHRs. The individual trial participant information is being obtained from Bristol Myers-Squibb. Using cohort methodology, estimates of the effect of apixaban vs warfarin on stroke, systemic embolism, myocardial infarction, major bleeding and mortality in the CPRD cohort of ARISTOTLE analogous patients will then be measured. The results will be compared with the ARISTOTLE findings to determine the utility of CPRD records for measuring medication effectiveness in AF. This objective will provide a methodological framework for measuring drug effectiveness in people with AF, using observational data from CPRD.

**Objective 2.** Extension of trial findings: Measure AF treatment effects in patients excluded from ARISTOTLE

Using the methodological template developed in Objective 1, we will determine the effect of apixaban vs warfarin in prevention of stroke, systemic embolism, myocardial infarction, major bleeding and mortality in people with AF not eligible for the ARISTOTLE study (most importantly people with substantial comorbidity), and look separately at important subgroups e.g. those with and without underlying cardiovascular disease.

**Objective 3.** Comparative effectiveness: Compare treatment effectiveness between multiple individual anticoagulants in all anticoagulant recipients (no eligibility criteria other than diagnosis of AF)

Using the methodological template developed in Objective 1, we will compare time to stroke, systemic embolism, myocardial infarction, major bleeding, and death based on prescribed treatments:

- a) warfarin
- b) apixaban

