- c) rivaroxaban
- d) dabigatran

Apixaban will be compared with warfarin then all other DOACs compared with apixaban.

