#### **o Censoring**

##### Index date

The index date for the EHR cohort will be the date of the patient's first prescription of apixaban or warfarin (for objectives 1 and 2), or for objective 3 first prescription of apixaban, warfarin, rivaroxaban, or dabigatran on or after the date the patient first met the eligibility criteria for the trial in the treatment period of interest

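### Objective 3 sets no first-use rule for rivaroxaban or dabigatran, so patients already on those drugs can enter the comparisons with apixaban, whose use is largely new

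*Protocol*

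**What the plan says.** Section E describes Objective 3 as having "no eligibility criteria other than diagnosis of AF" and plans the contrasts thus: "Apixaban will be compared with warfarin then all other DOACs compared with apixaban". Section M confirms that apixaban is compared with each of warfarin, rivaroxaban and dabigatran.

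On selection, section L says of Objective 3: "we will select all patients with AF with a prescription for any anticoagulant in the treatment period". Patients are then stratified by whether they would have met the ARISTOTLE criteria. The index date in section O is, "for objective 3 first prescription of apixaban, warfarin, rivaroxaban, or dabigatran on or after the date the patient first met the eligibility criteria". The criteria meant are those of ARISTOTLE, and the prescription must fall within the study window. No first-ever-use or washout condition is attached to rivaroxaban or dabigatran.

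The base cohort is "Patients with a prescription for an oral anticoagulant in the time period 01 January 2013 to 31 January 2019" with a prior AF diagnosis. The start date is tied to apixaban's UK authorisation for AF: "the minimum date is set to capture all patients prescribed apixaban for this indication in the UK". The only drug-specific prior-use exclusion anywhere is "no prior exposure to apixaban", which stands in the list of ARISTOTLE criteria under Objective 1.

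In section O (Regression model), the estimand admits continuing users for warfarin only, and the Cox model carries one prior-use term, prior warfarin/VKA status. The candidate matching variables in section L include concomitant use of an anticoagulant other than warfarin or apixaban.

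**The concern.** A patient indexed in the middle of treatment has already come through the early period in which bleeding, stroke or intolerance may have removed others from the drug. The protocol recognises a related mechanism: its Sensitivity analyses section notes that patients at higher bleeding risk may stop one treatment sooner than another.

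If one arm of a comparison consists largely of starters and the other includes such patients, part of the hazard ratio reflects the entry rule and not the drug. Covariates measured at the index date cannot bring back patients who left before it. At stake are the two head-to-head DOAC contrasts in Objective 3, for efficacy and for major bleeding. The Objective 1 validation against ARISTOTLE is not touched.

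**Working it through.** The protocol gives no sample size, event count or share of continuing users for Objective 3, so there is no figure of its own to reproduce. The check has two parts.

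**1. What the rules allow**

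- *Already on the drug when the window opens.* For apixaban in AF this is in effect closed off, because the window starts in the month of authorisation (section L). For rivaroxaban and dabigatran nothing closes it. The protocol gives no start dates for them, so whether such patients exist is an assumption.
- *On the drug before AF is coded or the criteria are first met.* The index date is the first prescription on or after eligibility, so an earlier prescription of the same drug does not prevent entry. In the trial-eligible stratum the prior-apixaban exclusion removes such apixaban patients, while a rivaroxaban or dabigatran patient in the same position stays in. Outside that stratum the route is open to all three DOACs.
- *Adjustment.* The prior-VKA term does not see earlier DOAC use. The concomitant-anticoagulant variable is only a candidate, and it does not record time already on the index DOAC. Section P commits to matching the arms for all objectives, but on baseline covariates of this kind.

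**2. Possible size (all inputs are assumptions)**

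Suppose the hazard in the first 3 months is k times the later hazard, a share p of the comparator arm is already past that period, follow-up is F years, and the true hazard ratio between starters is 1. Using average hazards, with the later hazard set to 1:

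- starters: N = (0.25k + F − 0.25)/F
- comparator arm: M = (1 − p)N + p
- inflation of apixaban/comparator: N/M

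For k = 2, p = 0.30:

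- F = 1: N = 1.25; M = 0.7 × 1.25 + 0.3 = 1.175; N/M = 1.064
- F = 2: N = 1.125; M = 1.0875; N/M = 1.034
- F = 3: N = 1.083; M = 1.058; N/M = 1.024
- F = 5 (the protocol's maximum): N = 1.05; M = 1.035; N/M = 1.014

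| k | p | F = 1 | F = 2 | F = 5 |
|---|---|---|---|---|
| 1.5 | 10% | 1.011 | 1.006 | 1.002 |
| 2 | 30% | 1.064 | 1.034 | 1.014 |
| 3 | 50% | 1.20 | 1.11 | 1.05 |

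A second formula makes no assumption about a 3-month period. If a share f of the comparator arm are continuing users with hazard r relative to starters, the observed ratio is 1/[(1 − f) + f·r]. It gives 1.005 (f = 5%, r = 0.9), 1.02 (f = 20%, r = 0.9), 1.11 (f = 20%, r = 0.5) and 1.25 (f = 40%, r = 0.5).

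With p or f = 0, or with k or r = 1, there is no distortion.

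**The case against.** A reader might infer that Objective 3 itself restricts apixaban to new users. It does not. The prior-apixaban exclusion is an Objective 1 criterion, and section E says Objective 3 has no criterion beyond AF. The exclusion reaches Objective 3 only through the trial-eligible stratum and through the index-date wording in section O, which conflicts with section E. Outside that stratum an apixaban patient treated before AF was coded can also be indexed mid-treatment. This stands: the asymmetry is firmest in the trial-eligible stratum, and elsewhere it rests mainly on the window start.

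A reader might also infer that the comparator arms do contain continuing users and that the contrasts are therefore biased against apixaban. The documents show only that the rules permit this. They give no share, no start dates for the other DOACs and no hazard by time on treatment, so both the existence and the direction of a bias are assumptions. The larger figures need short follow-up, a large share and a steep early hazard. One k for stroke, death and bleeding alike has no support in the text.

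The warfarin arm mixes starters and continuing users too, but there the protocol declares the mixture and adjusts for prior VKA use.

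Finally, Objective 3 is secondary to the Objective 1 validation and borrows its template, so extending the prior-drug exclusion to each DOAC could be called a clarification. That bears on weight. It does not remove the gap, because the selection and index-date rules are already written down and, followed as written, admit continuing users.

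**Conclusion.** The point holds in a limited form. Objective 3 has no first-use or washout rule for rivaroxaban or dabigatran, apixaban use is largely new, and no planned covariate captures time already on the index DOAC. Continuing users can therefore enter the two DOAC-versus-DOAC contrasts unadjusted.

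The size is unknown. If continuing users have a lower hazard than starters, the apixaban/comparator hazard ratio is pushed upward. For k = 2 and p = 30% this is about 6% over 1 year, falling to 1.4% over 5 years; across the assumed inputs it runs from well under 1% to 25%. That is reason to tighten the rule, not evidence that the planned result will be wrong.

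**What to change.** In section L (Objective 3) and in the index-date paragraph of section O, require the following for every DOAC arm, apixaban included, and in both strata: the index prescription is the patient's first recorded prescription of that DOAC, after at least 6 months of registration without it. Describe patients already on a DOAC at entry separately, with their number by drug, and keep them out of the comparative hazard ratios.

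In the same edit, reconcile section E (no criteria beyond AF for Objective 3) with section O (index date tied to meeting the trial criteria), so that it is clear which eligibility date starts the clock in each stratum.

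The cost is one eligibility sentence and one programming condition on prescription data the study already uses. The price is somewhat fewer patients, mainly in the rivaroxaban and dabigatran arms. If there are no continuing users, the exclusion of prior use removes nobody.
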